## Abstract

**Background:**

Obesity and type 2 diabetes mellitus are reaching epidemic proportions. In morbidly obese patients, bariatric operations lead to sustained weight loss and relief of comorbidities in the majority of patients. Laparoscopic Roux-Y-gastric bypass (RYGB) is one of the most frequently performed operations, but it is still unknown why some patients respond better than others. Therefore, a number of variations of this operation have been introduced. Recent evidence suggests that a longer bypassed biliopancreatic limb (BPL) has the potential to be more effective compared to the standard RYGB with a shorter BPL length. This article describes the design and protocol of a randomized controlled trial comparing the outcome of a RYGB operation with a long versus short BPL.

**Methods/design:**

The trial is designed as a multicenter, randomized, patient- and observer-blinded trial. The relevant ethics committee has approved the trial protocol. To demonstrate that long BPL RYGB is superior compared to short BPL RYGB in terms of weight loss and resolution of T2DM, the study is conducted as a superiority trial. Postoperative percent total weight loss and nutritional deficiency rate are the primary endpoints, whereas morbidity, mortality, remission of obesity-related comorbidities and quality of life are secondary endpoints. Eight hundred patients, between 18 and 65 years and with a body mass index (BMI) from 35 to 60 kg/m^2^ who meet the regulatory rules for bariatric surgery in Switzerland, will be randomized. The endpoints and baseline measurements will be assessed pre-, intra-, and postoperatively.

**Discussion:**

With its high number of patients and a 5-year follow-up, this study will answer questions about effectiveness and safety of long BPL RYGB and provide level I evidence for improvement of the standard RYGB. These findings might therefore potentially influence global bariatric surgery guidelines.

**Trial registration:**

ClinicalTrials.gov NCT04219787. Registered on 7 January 2020.

**Supplementary Information:**

The online version contains supplementary material available at 10.1186/s13063-021-05313-6.

## Background

The rising prevalence of morbid obesity is causing a major health burden in terms of morbidity and mortality [1]. Complications of obesity, especially type 2 diabetes mellitus (T2DM), are placing a growing demand on healthcare resources. The prevalence of T2DM increases parallel to obesity and currently; there are 55.2 million people with T2DM in Europe, accounting for 8.5% of the adult population [2]. About half of the obesity-associated healthcare costs in Switzerland are attributed to diabetes [3]. Morbid obesity is a chronic disease for which multimodal therapeutic management strategies are necessary, comparable to cancer treatment, to reach partial or full remission with a persistent risk of relapse and thus, long-lasting follow-up is mandatory. Medical therapeutic strategies (diet, behavioral changes, or drugs) to achieve and maintain clinically significant weight loss remain limited [4].

Bariatric surgery is currently the most effective treatment for morbid obesity [4–7]. Although laparoscopic sleeve gastrectomy has become the most commonly performed bariatric procedure worldwide [8], laparoscopic Roux-en-Y gastric bypass (RYGB) is the most frequently performed bariatric procedure in Switzerland. From a scientific point of view, it is no longer a question if this procedure has a significant effect on metabolic control, but rather how the outcomes after RYGB can be further improved.

Since its introduction in 1967 by Mason [9], there have been many multiple technical variations of the RYGB to increase weight loss. Most studies used an alimentary limb (AL) length of 100 to 150 cm and a biliopancreatic limb (BPL) length of 50 to 120 cm, while the common limb (CL) length remained not measured [10, 11].

Scopinaro et al. [12] developed the biliopancreatic diversion (BPD) technique in 1979 and concluded that the BPD seems to be the most powerful treatment for hyperlipidemia and T2DM. Available evidence suggests that the extended BPL length in patients after BPD may be one of the key factors explaining the superiority of this procedure, which is further supported by some observational studies reporting greater weight loss in patients after RYGB with a longer BPL [13–15].

To this day, only one randomized controlled trial (RCT) [16] compared long BPL RYGB (150 cm BPL, AL 75 cm) with a short BPL RYGB (BPL 75 cm, AL 150 cm) in 128 patients and found a significant increase in percent excess weight loss (%EWL) for patients with long BPL RYGB in the first 4 years after surgery. However, the underlying mechanism of a greater weight loss after long BPL RYGB remains unclear. Furthermore, lengthening of the BPL cannot be done limitless as it carries an increasing risk of severe malnutrition. Neither of the two procedures seems to be technically more challenging, since the complication rates did not show any significant difference [16]. However, a limitation of this study was the cohort of 146, which was too small to show any advantage in terms of comorbidities resolution or quality of life changes.

Therefore, our aim is to investigate if a longer BPL in RYGB leads to greater weight loss and superior remission of comorbidities in morbidly obese patients without reducing its safety. No matter which outcome will be obtained, our results will provide level I evidence for an improvement of the standard laparoscopic RYGB and thus may potentially influence global bariatric surgery guidelines.

## Methods/design

The overall objective of this study is to evaluate whether long BPL RYGB is superior compared to short BPL RYGB in treating morbid obesity and the associated comorbidities.

### Primary objective

The primary objective of this study is to show that long BPL leads to a greater percent total weight loss (%TWL, superiority), while not leading to a larger nutritional deficiency rate (non-inferiority) at 1-, 3-, and 5-year follow-up.

### Secondary objective

The secondary objectives are to assess the percent excess body mass index loss (%EBMIL), remission of comorbidities, complication rate/safety, and quality of life 1, 3, and 5 years after long and short BPL RYGB.

### Study design and site

This is a multicenter, randomized, controlled, patient- and observer-blinded, superiority trial in morbidly obese patients receiving either long BPL or short BPL RYGB. All participating centers (4 university hospitals and 11 cantonal, regional, and private hospitals) have knowledge and experience in bariatric surgery and were certified as Bariatric Reference Centers by the Swiss Society for the Study of Morbid Obesity and Metabolic Disorders (SMOB). The trial has been registered on ClinicalTrials.gov under the identifier NCT04219787. This protocol has been written in accordance with the Standard Protocol Items: Recommendations for Interventional Trials (SPIRIT) guidelines (Additional file 1). The planned visit and examination schedule is presented in Fig. 1.

**Fig. 1 Fig1:**
[figure not shown]
Schedule of enrollment, interventions, and assessments according to the Standard Protocol Items: Recommendations for Interventional Trials (SPIRIT) guideline

### Inclusion criteria

Participants fulfilling the following criteria are eligible for the study:
Informed consent (IC) as documented by signature (Appendix Informed Consent Form)Patients with BMI of 35 kg/m^2^ or higher who comply with the regulatory rules for bariatric surgery in Switzerland (SMOB guidelines [17])

### Exclusion criteria

The presence of any one of the following exclusion criteria will lead to exclusion of the participant:
Age < 18 years or > 65 yearsBMI > 60 kg/m^2^Height < 145 cmCL length of < 180 cm as measured intraoperativelyASA physical status classification > IIIPrevious bariatric operationInflammatory bowel diseaseOngoing malignant diseaseKnown or suspected non-compliance, drug or alcohol abusePsychiatric disorder

### Randomization

Eligible patients, who give written confirmed consent, will be registered in the electronic data capture and management system secuTrial®, which is programmed by the Clinical Trial Unit (CTU) of the University of Basel. The database is web-based and allows online randomization stratified by the involved centers. An allocation ratio of 1:1 with a block size of 4 will ensure a balance in sample size across both groups over time. The randomization allocation will only be known to the CTU staff. Patients will be enrolled and randomly assigned by the surgeon to receive a long BPL RYGB (arm A) versus a short BPL RYGB (arm B). Figure 2 provides a schematic view of both types of RYGBs.

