### Interventions

All patients will receive standard preoperative assessment including endocrine, pulmonary function and cardiovascular assessment, psychiatric assessment, gastroscopy with Helicobacter pylori testing, and abdominal ultrasound to check for liver size and gallstones. Patients in arm A will receive a RYGB with a 180-cm-long BPL and an AL of 80 cm; the group B will receive a RYGB with an 80-cm BPL and a 180-cm AL. The individual technique in terms of trocar position, materials used (i.e., staplers, trocar, suture) will be left to the choice of each individual surgeon. Total small bowel length will be measured during surgery; patients with a total small bowel length of less than 440 cm will be excluded from the study. Patient- and observer-blinded pre- and postoperative follow-up will be performed. There are no strategies for patients to improve adherence to intervention protocol since this is a surgical trial. All participating centers and surgeons are experienced bariatric surgeons with a minimal total caseload of more than 200 bariatric procedures and more than 50 surgeries per year. In order to make surgeons adhere to intervention protocol, all critical surgical steps (e.g., pouch size, total bowel length measurement, technique of Roux-limb and gastroenterostomy construction, closure of mesenteric defects, and operation time) will be documented in our database. The non-adherent cases will be excluded from per-protocol analysis. There will be no criteria for modifying the operative procedures.

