### Study visits

Physicians blinded to the intervention will perform study documentation and patient assessment. Since the trial is designed as an observer and patient blinded RCT, information about the surgical procedure will not be disclosed during the follow-up examinations to any assessors. There will be 11 study visits in total. The study design flow diagram is presented in Table 1. Potential study participants will be identified by the preoperative outpatient clinic consultations. The first visit will be preoperative after informed consent is obtained. Then patients will receive their study intervention according to the preoperative randomization. Postoperatively, study visits will be performed at discharge, 3, 6, 9, 12, and 18 months and 2, 3, 4, and 5 years. Each study visit includes data collection of weight, blood tests (e.g., hemoglobin, creatinine, urea, uric acid, calcium, C-reactive protein, albumin, liver function tests, fasting glucose, HbA1c, vitamins A, B1, B6, B12, and D, parathormone, ferritin, folate, zinc, cholesterol, lipoproteins, and triglycerides), and complications. In addition, questionnaires will be also assessed to study the quality of life (Bariatric Analysis and Reporting Outcome System [BAROS] [18] and the Gastrointestinal Quality of Life Index [GIQLI] [19]), the Arts questionnaire [20] to determine postoperative determine dumping syndrome and questionnaire for quantification of frequency and severity of potential diarrhea.

**Table 1 Tab1:** Schedule of study assessments

Study periods	Screening	Intervention	Follow-up								
Visit	1	2	3	4	5	6	7	8	9	10	11
Time (day, month, year)	− 3 months	0–5 days	3 months	6 months	9 months	1 year	1.5 years	2 years	3 years	4 years	5 years
Patient information and informed consent	x										
Demographics	x										
Medical history	x										
Inclusion/exclusion criteria	x	x									
Physical examination	x	x	x	x	x	x	x	x	x	x	x
Vital signs	x	x	x	x	x	x	x	x	x	x	x
Laboratory tests	x	x	x	x	x	x	x	x	x	x	x
Randomization		x									
Operation		x									
Complications		x	x	x	x	x	x	x	x	x	x
Primary variables	x	x	x	x	x	x	x	x	x	x	x
Secondary variables	x	x	x	x	x	x	x	x	x	x	x
Questionnaires	x			x		x		x	x	x	x
Adverse events		x	x	x	x	x	x	x	x	x	x

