### Blinding

With exception of the team in the operating theater, all involved medical and non-medical practitioners are blinded as well as the patient. The procedure will be named as *laparoscopic Roux-en-Y gastric bypass* in all medical records without mentioning the limb lengths. Unblinding is permitted at the end of the study and in case of surgical or medical complications, emergency consultation, or other ethical considerations. The operating surgeon will not be involved in any decisions that influence the primary endpoint or in judgement of the primary endpoint. Furthermore, the efficacy of blinding measures will be regularly assessed according to by Probst et al. [24].

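### A single, disclosed block size of 4 within centre, with the enrolling surgeon unblinded, lets up to a third of assignments be known in advance; undisclosed varying block sizes would be a cheap improvement

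*Protocol article*

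**What the plan says.** The Randomization section of the protocol article fixes three things.

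- Stratification: "The database is web-based and allows online randomization stratified by the involved centers".
- Blocks: "An allocation ratio of 1:1 with a block size of 4 will ensure a balance in sample size across both groups over time". One size is given, no variation is mentioned, and the size is printed in a public article.
- Who does it: "Patients will be enrolled and randomly assigned by the surgeon". The same section says of concealment: "The randomization allocation will only be known to the CTU staff".

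The Blinding section adds: "With exception of the team in the operating theater, all involved medical and non-medical practitioners are blinded as well as the patient". The surgeon has to know the limb lengths to build them, so the role that enrols is also the role that learns the arm.

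On timing, the Study visits section says: "Then patients will receive their study intervention according to the preoperative randomization". Table 1 puts consent at visit 1, three months before surgery, and randomization at visit 2. Entry criteria are checked at both visits. The Exclusion criteria include items that call for judgement, among them suspected poor compliance.

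**The concern.** Permuted blocks of one small, known size leave a trace. Once the earlier allocations in a block are known, the remaining ones are constrained and sometimes fixed. Keeping the list at the trial unit does not help against someone who sees the allocations as they are carried out and can count to four. Here that person may also be the one who decides whether the next candidate enters, and when.

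At stake is comparability of the arms. A surgeon who expects the next arm could enrol, postpone or decline a patient on features already known, such as BMI within the permitted 35 to 60 kg/m² or an impression of likely compliance. These features plausibly relate to weight loss and to nutritional deficiency, the two primary endpoints. The selection would happen before randomization. Blinded patients and assessors cannot undo it, and analysing patients as randomized only preserves whatever groups were formed.

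**Working it through.** The article states no predictability figure, so there is none to reproduce. The sample size of 400 per group does not depend on the block size and is not in question here.

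**Inputs.** Block size 4, ratio 1:1, stratified by centre (Randomization); 15 centres, 4 + 11 (Study design and site); 800 patients (Abstract). The number of surgeons per centre is not stated, so it is varied below.

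**Step 1: one observer who knows the block size and every earlier allocation at the centre.** With L for long and S for short biliopancreatic limb, six blocks are equally likely: LLSS, LSLS, LSSL and their mirror images.

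| Position in block | Chance that the assignment is certain | Chance that the best guess is right |
|---|---|---|
| 1 | 0 | 1/2 |
| 2 | 0 | 2/3 |
| 3 | 1/3 (first two agree) | 1/3 × 1 + 2/3 × 1/2 = 2/3 |
| 4 | 1 | 1 |

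Certain share: (0 + 0 + 1/3 + 1)/4 = 33.3%. Best guess: (1/2 + 2/3 + 2/3 + 1)/4 = 70.8%, against 50% by chance. For 800 patients, 800/3 is about 267 certain assignments. With equal recruitment over 15 centres (assumption), 800/15 is about 53 patients per centre, of which about 18 are certain.

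**Step 2: k surgeons share one centre list equally and exchange nothing (assumption).** Each sees only the arms of his or her own patients but knows how many patients the centre has randomized. An assignment is certain only if both earlier patients of the completed arm were that surgeon's own, which has probability 1/k². So position 3 contributes (1/3)/k² and position 4 contributes 1/k². The certain share is (4/3)/(4k²) = 1/(3k²).

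- k = 1: 33.3%
- k = 2: 1/12 = 8.3%, about 67 of 800
- k = 3: 1/27 = 3.7%, about 30 of 800

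A simulation of the same setting gave 33.3%, 8.3% and 3.7%.

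**Step 3: alternatives, for the fully informed observer of step 1.** A fixed size 2m gives a certain share of 1/(m + 1). The mixed sizes were simulated with 60 patients per centre and 4,000 repetitions, each size equally likely. The observer knew the possible sizes but not their order.

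| Scheme | Certain | Best guess right |
|---|---|---|
| Fixed 4 (plan) | 33.3% | 70.8% |
| Fixed 6 | 25.0% | 68.3% |
| Fixed 8 | 20.0% | 66.6% |
| 4 and 6 mixed | 5.6% | 69.1% |
| 4, 6 and 8 mixed | 2.4% | 67.8% |

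Mixing removes most of the certainty (33.3% to 2.4%, or about 267 to 19 of 800) but little of the guessing advantage (70.8% to 67.8%). The largest imbalance within a centre is half the largest block: 2 patients with size 4, and 4 with sizes up to 8.

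**The case against.** The strongest reply is that the article never says surgeons see every allocation. Only the team in theatre is unblinded, and medical records name the operation without limb lengths. A surgeon who did not operate on a case is therefore meant not to know its arm. This stands: 33% is a ceiling, reached where one surgeon operates on all cases or colleagues tell each other. A reader might take it as the rate for the whole trial, which the documents do not support. They also describe nothing that stops colleagues in one unit from exchanging the information.

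A reader might add short bowel to the features that can be steered. That does not follow. Bowel length is measured in theatre, after preoperative randomization, so it is unknown when the next assignment is being predicted. By the time it is known, the arm is already assigned and needs no prediction. Exclusion after allocation by an unblinded surgeon is a separate issue, present under any block size.

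A reader might also see a contradiction in "The randomization allocation will only be known to the CTU staff". The sentence reads naturally as concealment of the list of future assignments. It cannot cover allocations already carried out, but that is loose wording rather than a separate error.

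Safeguards exist. Randomization is central and online, after consent and registration. The Analysis of endpoints section plans to compare suitable patients who were not included with those who were, overall and by arm. That can reveal selection on recorded characteristics, though it neither prevents selection nor sees unrecorded judgements. Suspected poor compliance is an exclusion in both arms, which limits that route. Because it is a judgement, it could still be applied more or less strictly according to the expected arm.

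Finally, varying block sizes lower the best-guess rate by only about three percentage points. That is true. The gain is in certainty, and it is smaller where several surgeons share a list without exchanging information.

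**Conclusion.** The point holds as a cheap improvement. A single, disclosed block size of 4 within centre, combined with an enrolling surgeon who is unblinded, lets past allocations reveal future ones. Up to 33% of assignments can be known with certainty and 71% guessed correctly by someone who knows all earlier allocations at the centre. The certain share is about 8% or 4% if two or three surgeons share the list equally and exchange nothing. Where a given centre lies in this range cannot be read from the article.

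The 33% assumes complete blocks and knowledge of the block size. The per-centre count assumes equal recruitment. A reader might infer that both primary endpoints are in fact biased. The documents give no evidence of steering and no basis for a direction or size of bias. What is established is an avoidable opportunity for selective enrolment on features known before randomization.

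**What to change.** For blocks not yet used, have the clinical trial unit program randomly varying block sizes within centre, for example 4, 6 and 8. Withhold the sizes from sites and leave them out of site-facing documents. It would also help to reword the concealment sentence so that it plainly refers to the list of future assignments.

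The cost is a configuration change in the randomization system and a maximum within-centre imbalance of 4 instead of 2 patients, which is minor at about 53 patients per centre. Enrolment was planned to start in June 2020 and last two to three years, so the change protects only what is still to be allocated. If all blocks have been used, the fixed size should be reported as a limitation.

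The change does not address intraoperative exclusion after allocation, which needs separate consideration.

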**Fig. 2 Fig2:**
[figure not shown]
Enrolled patients receive a Roux-en-Y gastric bypass either with long biliopancreatic limb (BP-limb) and short alimentary limb (A-limb) or short biliopancreatic limb and long alimentary limb (A-limb). The common limb (C-limb) should remain the same for both groups

### Interventions

All patients will receive standard preoperative assessment including endocrine, pulmonary function and cardiovascular assessment, psychiatric assessment, gastroscopy with Helicobacter pylori testing, and abdominal ultrasound to check for liver size and gallstones. Patients in arm A will receive a RYGB with a 180-cm-long BPL and an AL of 80 cm; the group B will receive a RYGB with an 80-cm BPL and a 180-cm AL. The individual technique in terms of trocar position, materials used (i.e., staplers, trocar, suture) will be left to the choice of each individual surgeon. Total small bowel length will be measured during surgery; patients with a total small bowel length of less than 440 cm will be excluded from the study. Patient- and observer-blinded pre- and postoperative follow-up will be performed. There are no strategies for patients to improve adherence to intervention protocol since this is a surgical trial. All participating centers and surgeons are experienced bariatric surgeons with a minimal total caseload of more than 200 bariatric procedures and more than 50 surgeries per year. In order to make surgeons adhere to intervention protocol, all critical surgical steps (e.g., pouch size, total bowel length measurement, technique of Roux-limb and gastroenterostomy construction, closure of mesenteric defects, and operation time) will be documented in our database. The non-adherent cases will be excluded from per-protocol analysis. There will be no criteria for modifying the operative procedures.

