#### Analysis of endpoints

The study results will be reported in adherence to the extension of the CONSORT statement from 2010 on reporting of randomized trials [25]. Summary statistics will be used to describe and compare patient characteristics of all suitable, but non-included patients and all included patients (overall and stratified for the two treatment arms). Study endpoints will be analyzed for the intention-to-treat (ITT) population and the per-protocol (PP) population. Sensitivity analysis will be conducted for the ITT population. Thereby, the ITT population includes all randomized patients in the groups to which they were randomly assigned, regardless of their adherence with the entry criteria, regardless of the treatment they actually received, and regardless of subsequent withdrawal or deviation from the protocol. In the PP population, all protocol violators, including anyone who switched groups or missed measurements, are excluded. For each group, a number of participants (denominator) included in each analysis and whether the analysis was by original assigned groups will be given. Additional sensitivity analysis will be used if, despite all efforts taken to ensure complete data collection, the number of missing data is non-negligible or could potentially bias the results and conclusions.

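### Patients are randomised before surgery but can be excluded from the study on a length measured during surgery, which does not fit the ITT definition and leaves arm-dependent exclusion possible

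*Protocol article*

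**What the plan says.** Four parts of the protocol article bear on this point.

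- **Timing of randomisation.** Study visits states that "patients will receive their study intervention according to the preoperative randomization". Table 1 lists the second eligibility check, randomisation and the operation under visit 2 without giving their order.
- **Exclusion in theatre.** Exclusion criteria lists a common limb (CL) shorter than 180 cm, measured at operation. Interventions says that total small bowel length is measured during surgery and that "patients with a total small bowel length of less than 440 cm will be excluded from the study".
- **Who knows the arm.** Blinding states: "With exception of the team in the operating theater, all involved medical and non-medical practitioners are blinded as well as the patient". Under Randomization, the surgeon enrols and assigns the patient through the web-based system.
- **Analysis set.** Analysis of endpoints says that "the ITT population includes all randomized patients in the groups to which they were randomly assigned, regardless of their adherence with the entry criteria". It adds that this holds whatever treatment was received and despite later withdrawal or deviation.

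**The concern.** A criterion that can be checked only in theatre is applied to patients who have already been randomised, and those who fail it leave the study. The ITT definition counts them as analysed. If they are not followed, the ITT set exists on paper but part of its endpoint data is never collected, and no later analysis can recover it.

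The second issue is knowledge of the arm. The length is measured by a team that must know the assigned limb lengths in order to build them. If a borderline measurement were treated differently according to the arm, exclusion would depend on allocation. For nutritional deficiency, losing the more vulnerable patients from the long-limb arm alone would lower that arm's rate and make non-inferiority easier to show.

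**Working it through.** **1. Do the two length rules agree, and do they depend on the arm?** Limb lengths are from Interventions and the CL limit from Exclusion criteria.

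- Arm A: biliopancreatic limb (BPL) 180 + alimentary limb (AL) 80 + CL 180 = 440 cm
- Arm B: BPL 80 + AL 180 + CL 180 = 440 cm

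The CL rule and the total-length rule are the same rule, and the cut-off does not depend on the arm. BPL and AL together take 260 cm in either arm, so eligibility can be checked without knowing the allocation.

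**2. Can the passages be read together?** The exclusion could be harmless in two ways.

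- It might mean removal from the per-protocol set only. But Interventions separately says that non-adherent cases leave the per-protocol analysis, while the length rule removes patients from the study. The two phrases differ within one paragraph.
- The length might be measured before the arm is disclosed. Table 1 would allow this, but Study visits gives the only stated order and puts randomisation first. Randomization says that only the clinical trial unit's staff know the allocation, but that cannot hold once the theatre team builds the assigned limbs.

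No other section reconciles the statements.

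**3. The plan's own sample size.** Inputs from Sample size: deficiency rate 50% in each arm, margin 10% (read as absolute), power 80%, alpha 5% (read as two-sided, so 2.5% one-sided).

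n per arm = (1.960 + 0.842)² × (0.5×0.5 + 0.5×0.5) / 0.10² ≈ 393

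This reproduces the planned 400. Slack is 400 − 393 = 7 per arm, or 1.75%. The weight-loss comparison (5 points, SD 10) needs only about 63 per arm by a comparison of means, so non-inferiority drives the sample size.

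**4. Loss of patients equally in both arms.** The document gives no exclusion rate, so the rates below are assumptions. Power = Φ(0.10 / √(0.5/n) − 1.960).

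| Assumed loss | n per arm | Power |
|---|---|---|
| 0% | 400 | 80.7% |
| 2% | 392 | 80.0% |
| 5% | 380 | 78.7% |
| 10% | 360 | 76.5% |

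**5. Extra loss from arm A only.** The true rate is set at 50% in both arms. A fraction f of arm A, with deficiency risk r, is removed. Both f and r are assumptions.

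Observed arm A rate = (0.50 − f × r) / (1 − f)

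- f = 5%, r = 80%: (0.50 − 0.04) / 0.95 = 48.4%, a shift of −1.6 points
- f = 10%, r = 80%: (0.50 − 0.08) / 0.90 = 46.7%, a shift of −3.3 points
- With r from 60% to 100%, the shift is 0.5 to 2.6 points for f = 5%, and 1.1 to 5.6 points for f = 10%.

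**The case against.** Most of the opposing case concerns scope and size, and much of it stands.

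- **The rule is numeric and arm-neutral.** Bowel length is a pre-treatment characteristic that allocation cannot change. Applied evenly, the rule narrows the population without biasing the comparison. The length measurement is also documented in the database, and the trial is monitored centrally and on site. This stands: bias requires uneven measurement or judgement, which the document permits but does not show.
- **The decision-maker is not named.** That the surgeon decides the exclusion is an inference, though a fair one, because the measurement is made in theatre.
- **Loss of follow-up is not stated.** By the ITT definition these patients belong to the set, and additional sensitivity analysis is foreseen for missing data. The full protocol may say more. This stands in part: the open question is whether their data are collected, and the wording used suggests that they are not.
- **The illustration needs a large effect.** An extra 5% to 10% from one arm means 20 to 40 of 400 patients excluded by discretion. Even then the shift at 80% risk is 1.6 to 3.3 points.

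A reader might also infer a conflict with the statement in Blinding that "The operating surgeon will not be involved in any decisions that influence the primary endpoint". The document does not support this. The sentence goes on to the judging of the primary endpoint, and the section expressly exempts the theatre team from blinding. Applying an entry criterion is not an endpoint decision, and on so literal a reading even constructing the limbs would be a breach.

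**Conclusion.** The contradiction stands: randomisation before surgery, removal from the study on a measurement made during surgery, and an ITT set of all randomised patients are not reconciled anywhere in the article. Randomised patients may therefore lack the endpoints that the ITT analysis needs.

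It would go too far to say that the randomised comparison is broken on both primary endpoints. Arm-dependent exclusion is a possibility left open by the unstated order of measurement and disclosure. For weight loss, neither a direction nor a size can be derived.

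The size of the problem is unknown. The 48.4% and 46.7% figures rest on assumed exclusion fractions and an assumed 80% deficiency risk; the power figures rest on assumed losses and the two-sided reading of alpha. The contradiction itself depends on none of these.

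**What to change.** Reconcile Exclusion criteria, Interventions, Study visits and Analysis of endpoints with one rule for all centres. A mixture would give some centres a randomised population that includes short-bowel patients and others one that does not.

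- **Preferred.** Release the allocation in secuTrial only after the measured length has been entered in theatre and eligibility confirmed. Amend the sentence in Study visits that places randomisation before the operation, and state the order of steps within visit 2.
- **Otherwise.** State that every randomised patient stays in follow-up and in the ITT set, and that the length criterion removes patients from the per-protocol set only. For anyone already randomised before surgery, this is the only route left.

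The preferred route costs one web entry in theatre and a small amendment, with no extra procedures; the 800 would then be patients who have passed the length check. The alternative costs the scheduled follow-up of patients who would otherwise have left. Neither implies any view on the cut-off or on which operation a patient below it should receive.
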